### Study Design, Setting, and Sample

This study will use a pre-post, nonrandomized, 6-month longitudinal intervention design, implemented using questionnaires and semistructured interviews (Figure 2). Enrollment will occur through the Augusta University Sickle Cell Center’s satellite clinic, Phoebe Putney Cancer Center, in Albany, Georgia. This site has not previously worked with a CHW, either directly or through a community-based organization.

Eligible participants will be adults with SCD aged 18‐45 years. Given the target sample size (n=40), at 80% power and α=.05, we can detect small to moderate effect sizes (*r*^2^=0.4 to 0.6) using a 2-tailed paired *t* test [22]. This sample includes an expected 20% attrition rate. There are currently 97 eligible individuals seeking SCD care at this location. This is more than double the expected enrollment of 30 participants. Using a rolling recruitment process, the PI will work with MTS to enroll additional participants if an enrolled participant is lost to follow-up. The assumption of a small to moderate effect is conservative, given that studies designed to improve self-care in SCD report a medium effect size (*d*=0.71) [8,23].

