### Study Procedures

Adults with SCD (aged 18‐45 years) will be recruited from the Augusta University Sickle Cell Center’s satellite clinic in Albany, Georgia. Clinic staff will identify participants who meet the inclusion criteria. For eligible patients, clinic staff will describe the study and offer participation during the patient’s regularly scheduled clinic visit. During the visit, interested patients will provide written informed consent and the link to the baseline questionnaire to be completed via Qualtrics. Each participant will receive a $20 gift card after completing the questionnaires. Following enrollment, participants will be referred to MTS for assignment to a CHW.

The CHW will schedule an initial session (60 minutes) with participants, followed by 5 subsequent monthly sessions (virtual or telephone-based) scheduled for 30 to 60 minutes, for a maximum of 6 patient contact hours over 6 consecutive months. During each monthly session, the CHW will educate participants on SCD management (ie, preventive services, management of acute complications, and management of chronic complications). The CHW will use a subjective, objective, assessment, and plan (SOAP) format for reporting via Qualtrics. The SOAP form is a standardized documentation method used by health care providers to systematically record patient information, thereby enhancing communication about health care experiences [24]. By organizing patient encounters into 4 distinct sections, the SOAP note serves as a clear framework for evaluating patient data and outlining management strategies [24]. This report will allow the CHW to document observations from patient interactions.

After completion of the sixth and final session, the CHW will provide a link to the postintervention questionnaire to be completed via Qualtrics. The postintervention questionnaire contains a question of interest about participating in debriefing interviews. We will conduct semistructured debriefing interviews with patients (n=35 approximately) to determine the perceived feasibility and acceptability of the study procedures. A member of the research team will conduct the interviews using a semistructured interview guide. Interviews are expected to last 45 to 60 minutes, and compensation will be a US $25 gift card. All incentives will be distributed by the PI per the institutional review board–approved protocol for research involving human subjects.

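### About 35 patient interviews do not fit the 32 completers expected from 40 enrolled, and the only invitation described reaches completers who volunteer

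*Protocol article*

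**What the plan says.** Study Procedures (Protocol article) gives the number of patient interviews: "We will conduct semistructured debriefing interviews with patients (n=35 approximately) to determine the perceived feasibility and acceptability of the study procedures". It also gives the way in. The community health worker (CHW) sends the post-intervention questionnaire link once the sixth and last session is done, and "The postintervention questionnaire contains a question of interest about participating in debriefing interviews". No other patient invitation is described.

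Study Design, Setting, and Sample gives the figures that determine how many people reach that point. The target is stated as "Given the target sample size (n=40), at 80% power and α=.05", followed by "This sample includes an expected 20% attrition rate". The pool is described as "There are currently 97 eligible individuals seeking SCD care at this location", and the next sentence reads "This is more than double the expected enrollment of 30 participants". The section also provides for replacement: the investigator will work with the community organisation to "enroll additional participants if an enrolled participant is lost to follow-up". No cap on replacement is given.

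Acceptability among patients and care team members is the third specific aim in the Introduction. Acceptability among participants is the fourth feasibility criterion in Procedures and Data Collection, beside enrolment, retention and intervention completion. Acceptability of the Intervention adds interviews with 2 CHWs and 3 clinic staff, on top of the patient interviews.

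**The concern.** There are two linked problems.

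The first is numerical. An interview count should follow from the number of people who reach the invitation and the share who accept. Here the planned count is larger than the expected number who reach it, before anyone declines. The plan also carries two enrolment figures, 40 and 30, so the reader cannot tell which base the 35 was set against. It fits neither.

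The second concerns who is heard. The invitation sits on a questionnaire issued after the last session, so a participant who stops earlier does not meet it. The interviews are meant to cover ease of use, helpfulness, time required and rapport with the CHW. These are plausible reasons for stopping, and people who stopped for them are outside the sample. The Results section relies on the debriefing interviews to find improvements before a larger study. For that purpose, the accounts of those who left are among the most informative.

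**Working it through.** **Inputs, all from the protocol article**
- Planned patient interviews: about 35 (Study Procedures).
- Target sample: 40, with 20% attrition included (Study Design, Setting, and Sample).
- Conflicting enrolment figure: 30 (same section).
- Eligible pool: 97, with replacement of lost participants allowed (same section).
- Opt-in rate among completers: not stated. It is varied below as an assumption.

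**Step 1. Expected completers = N × (1 − attrition).**
- N = 40: 40 × 0.80 = 32. Reverse check: 32 / 0.80 = 40, which agrees with a target that already includes attrition.
- N = 30: 30 × 0.80 = 24.

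**Step 2. Compare with 35.** The figure is not reproduced from either base.
- 35 − 32 = 3; 35 / 32 = 1.09.
- 35 / 24 = 1.46; 35 / 30 = 1.17, so 35 exceeds that enrolment even with no attrition.

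**Step 3. Chance variation without replacement.** If completion is binomial with 40 participants and probability 0.80, P(at least 35 complete) = 0.16, before any refusal.

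**Step 4. Effect of opt-in, no replacement.** Expected interviews = completers × opt-in. Enrolment needed for 35 = 35 / (0.80 × opt-in), rounded up.

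| Assumed opt-in | Interviews from 32 completers | Interviews from 24 completers | Enrolment needed for 35 |
|---|---|---|---|
| 100% | 32 | 24 | 44 |
| 90% | 29 | 22 | 49 |
| 80% | 26 | 19 | 55 |
| 70% | 22 | 17 | 63 |

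**Step 5. Effect of replacement.** If lost participants are replaced until 40 finish, the opt-in needed is 35 / 40 = 87.5%. At 20% attrition this means enrolling about 40 / 0.80 = 50 people, within the pool of 97.

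**Step 6. Who is not sampled.** Expected early stoppers are 40 × 0.20 = 8 (or 30 × 0.20 = 6). Under the described route none of them is invited. Replacement adds further completers but does not bring these people in.

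**The case against.** *Replacement and the word approximately.* A reader might infer from step 1 that 32 is a maximum and 35 cannot be reached. The document does not support that. The 32 is an expectation, the same section allows lost participants to be replaced from 97 eligible people, and the 35 is labelled approximate. With 40 finishers the number is reachable at 87.5% opt-in, and more enrolment would lower that rate. This answers the claim of impossibility. It does not reconcile the three figures, and it does nothing for the selection.

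*Satisfied completers.* A reader might also infer that acceptability will be judged only by satisfied patients. Satisfaction plays no part in the described selection, which is by completing and volunteering. Dissatisfied people can finish, the US $25 card gives them a reason to take part, and the interviews ask for suggestions for improvement. Upward bias is the plausible direction, not an established fact.

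*Other sources.* CHWs and clinic staff are also interviewed, retention and completion are separate criteria, and the CHW reports to the investigator after each visit, partly to catch likely dropout. So completers are not the only source on acceptability and feasibility. But counts of dropouts do not explain them, and a CHW's account cannot replace the patient's own view of that CHW.

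*A condensed article.* The text does not say that nobody else may be invited, the flowchart is not shown, and the full protocol may describe contact with those who stop. This limits the second half of the point to the mechanism as described. That mechanism is stated, however, and it excludes early stoppers.

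*A possible origin of the number.* 30 + 2 + 3 = 35 would match 30 patients plus the CHWs and clinic staff. This is conjecture: the article assigns 35 to patients and presents the others as additional.

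**Conclusion.** The point holds in this form: about 35 patient interviews are inconsistent with the plan's own expected completers, by 3 if 40 enrol (109% of 32) and by 11 if 30 enrol (146% of 24). On the stated expectations, reaching 35 takes replacement of dropouts together with very high opt-in, 87.5% if 40 finish. As described, patient-reported acceptability comes only from completers who volunteer, and the expected one in five who stop early are not sampled.

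The arithmetic rests on the stated 20% attrition. The opt-in rates are assumptions, because the article gives none. The upward direction of the bias is an inference and its size cannot be estimated from the document. The numerical half is firmer than the selection half, since an unseen full protocol could contain a route for non-completers. The point is a worthwhile and inexpensive improvement; it does not invalidate the study.

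**What to change.** 1. Reconcile the 40, the 30 and the 35. State one enrolment figure, say whether replacements count within it, and give any cap on replacement.
2. Restate the number of patient interviews so that it follows from the reconciled enrolment, attrition and replacement, and from an opt-in rate labelled as an assumption. A fixed ceiling of 32 would be wrong: it ignores replacement and would conflict with item 3, under which people who do not complete can also be interviewed.
3. Have the research team extend the interview invitation, with the same guide and the same US $25 card, to all enrolled participants who have not withdrawn consent to contact, including those who stop sessions. If the full protocol already does this, say so in the article.
4. Report acceptability separately for completers and non-completers, with the number invited and the number interviewed in each group.

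The cost is text changes and a few extra contacts (about 8 expected early stoppers among 40), within the interview budget already planned for about 35. Contacting people who stopped early may need a minor ethics amendment. With 16 enrolled as of March 2026, 40 − 16 = 24 of the target would still enter under the revised procedure.

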### Measures

#### Overview

Eligible patients will be referred to MTS for assignment to a CHW. At the initial session, participants will complete a baseline survey assessing patient satisfaction and self-report self-care behaviors. We will use a demographics questionnaire, the Medical Outcomes Study Patient Satisfaction Questionnaire [25], and the Jenerette Self-Care Assessment Tool [20] (refer to Multimedia Appendix 1 for details). The CHW will complete a SOAP report at each session, documenting observations of the participant’s condition and responses related to self-care behaviors. After each visit, the CHW will report the results to the PI. These sessions will allow the PI to assess study fidelity and address any challenges with implementation or potential participant dropout. It will also allow the research team to determine whether modifications to the program are needed to ensure participant retention. During the final CHW session, the participant will complete a postintervention survey on patient satisfaction and self-report self-care behaviors.

Patient satisfaction with medical care will be assessed using the Medical Outcomes Study’s Patient Satisfaction Questionnaire Short Form (PSQ-18) [25]. The PSQ-18 is an 18-item self-report instrument designed to evaluate patients’ satisfaction with health care services across multiple domains, including general satisfaction, technical quality, interpersonal manner, communication, financial aspects, time spent with providers, and accessibility and convenience. Items are rated on a 5-point Likert scale ranging from strongly disagree to strongly agree. Subscale scores are computed by averaging item responses, with higher scores indicating greater satisfaction with care. The PSQ-18 has demonstrated good reliability and validity across diverse patient populations and is widely used in health services research [25].

SCD-specific self-care behaviors will be assessed using the Jenerette Self-Care Assessment Tool [20]. This instrument was developed to evaluate self-care management behaviors among individuals with SCD, including symptom monitoring, pain management, medication adherence, and engagement in health-promoting behaviors. The tool consists of multiple self-report items rated on a Likert-type scale, with higher scores indicating greater engagement in effective self-care behaviors. The Jenerette Self-Care Assessment Tool has demonstrated acceptable reliability and validity and has been used in previous studies examining self-care management among adults with SCD [20].

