### Ethical Considerations

This protocol will be conducted in accordance with the Declaration of Helsinki. Ethics approval has been granted on an expedited basis by the institutional review board of Georgia Southern University (H21406) for surveys and interviews conducted with human subjects. Informed consent will be obtained from all participants, who will then receive a link to the baseline questionnaire to be completed via Qualtrics XM (Silver Lake and CPP Investments). Each participant will receive a US $20 gift card after completing the questionnaire.

Health Insurance Portability and Accountability Act (HIPAA)–protected information will not be discussed during calls. Information collected during calls will be stored on a cloud server that is only accessible to the research team. To protect the confidentiality of participants, each of them will be assigned a unique participant code.

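### The protocol places each primary-outcome survey on two different occasions: baseline at consent or at the first CHW session, post-intervention after or during the last session

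*Protocol article*

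**What the plan says.** **Baseline.** Two sections of the protocol article attach it to consent. Ethical Considerations: "Informed consent will be obtained from all participants, who will then receive a link to the baseline questionnaire". Study Procedures, describing the clinic visit: "During the visit, interested patients will provide written informed consent and the link to the baseline questionnaire to be completed via Qualtrics". Study Procedures then puts the hand-over to the community organization later: "Following enrollment, participants will be referred to MTS for assignment to a CHW". The Measures overview reverses the order. It begins with referral to MTS and assignment to a CHW, and continues: "At the initial session, participants will complete a baseline survey assessing patient satisfaction and self-report self-care behaviors".

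**What the initial session is.** Study Procedures: "The CHW will schedule an initial session (60 minutes) with participants, followed by 5 subsequent monthly sessions". On content, the same section says: "During each monthly session, the CHW will educate participants on SCD management".

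**Post-intervention.** Study Procedures: "After completion of the sixth and final session, the CHW will provide a link to the postintervention questionnaire to be completed via Qualtrics". Procedures and Data Collection agrees in substance, since it places the second assessment after the 6-month intervention. The Measures overview says: "During the final CHW session, the participant will complete a postintervention survey on patient satisfaction and self-report self-care behaviors".

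**Use of the two surveys.** Patient satisfaction and self-care behaviors are the primary outcomes, both by self-report. The design is pre-post and nonrandomized, no comparison group is described, and Data Analysis compares the two time points with paired t tests.

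**The concern.** The quantitative effectiveness result rests on the difference between two questionnaires, and the protocol gives two occasions for each of them. A baseline completed once CHW contact or education has begun is no longer a clean pre-intervention value. A post survey completed during a CHW session may be answered in contact with the person who has delivered the intervention for six months, which invites favorable answers on self-report scales.

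These effects tend in opposite directions, and they may differ between participants or between the two CHWs, depending on which section was followed. A comparison group would share at least some of such artefacts. Here there is none, so any shift caused by timing or setting goes straight into the estimated change.

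**Working it through.** No figure in the protocol is in dispute, so there is none to reproduce. The main check is to set the texts side by side.

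| Time point | Ethical Considerations | Procedures and Data Collection | Study Procedures | Measures overview |
|---|---|---|---|---|
| Baseline | link follows consent | at baseline, occasion not specified | link given with consent at the clinic visit; MTS referral comes later | completed at the initial session, after MTS referral |
| Post | not addressed | after the intervention | link sent after session 6 is complete | completed during the final session |

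*Baseline.* Study Procedures fixes when the link is given, not when the form is filled in. Link at the clinic and completion at session 1 is therefore a possible joint reading. But it would mean that nothing requires the baseline to precede CHW contact, and the Measures overview does not say whether the form comes before or after the education in that session.

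*Post.* Completion during session 6 and a link sent only after session 6 cannot both be followed.

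**Scale of an upward reporting shift (illustration).**

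Inputs:
- Two-sided α = 0.05, from Study Design, Setting, and Sample.
- n = 40 × (1 − 0.20) = 32 pairs, from the target of 40 and the 20% attrition in that section. The section also mentions an expected enrollment of 30, which gives 30 × 0.80 = 24 pairs.
- A net reporting shift δ, in SDs of the paired differences, with no true change. The protocol gives no value; 0.2 and 0.3 are assumptions.

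The rejection probability of the paired t test is P(|T| > t(0.975, n − 1)), where T is noncentral t with n − 1 degrees of freedom and noncentrality δ√n.

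| n | δ | δ√n | P(significant) |
|---|---|---|---|
| 32 | 0.2 | 1.131 | 0.195 |
| 32 | 0.3 | 1.697 | 0.376 |
| 24 | 0.2 | 0.980 | 0.156 |
| 24 | 0.3 | 1.470 | 0.291 |

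The unit matters. If the shift s is in SDs of the score itself, with equal SDs at both times and pre-post correlation r, then δ = s / √(2(1 − r)). With n = 32 and s = 0.2 or 0.3, the probabilities are 0.153 and 0.285 at r = 0.3, and 0.293 and 0.565 at r = 0.7. The protocol gives no correlation.

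**Scale of a late baseline (illustration).** Suppose a share f of the true effect d is already in the baseline score. The detectable effect becomes d(1 − f). With n = 32:

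| d | f = 0 | f = 0.10 | f = 1/6 |
|---|---|---|---|
| 0.5 | 78% | 69% | 63% |
| 0.6 | 91% | 84% | 78% |
| 0.71 | 97% | 94% | 90% |

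Here 0.71 is the effect size the protocol cites, treated as a paired effect; 0.5, 0.6 and both values of f are assumptions (1/6 stands for one session of six).

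**The case against.** The best defense is that little of the harm is written down. The Measures overview does not say that the baseline follows education; a form completed as session 1 opens would precede it. Nor does it say that the CHW administers the survey or sees the answers, and Study Procedures describes both questionnaires as Qualtrics forms reached by a link. All other sections that address timing agree, so the Measures overview may simply be loosely worded. If it were followed at both time points, the CHW's presence would be common to both surveys and only its differential part would bias the change.

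All of this stands, and it limits the claim. A reader might infer that the surveys are answered with the CHW listening, or that education has already been given when the baseline is taken. Both are possible under the text, but neither is stated. A reader might also expect practice to vary between sites; the protocol has one enrolling clinic, so any variation would be between participants or CHWs. Finally, the 20% and 38% might be read as the study's false-positive rate. They are not: they apply only to an assumed net upward shift in SDs of the paired differences with 32 pairs.

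The defense does not remove the conflict. The two post-survey instructions are incompatible, and no section requires the baseline to be complete before CHW contact. An analysis plan cannot repair this afterwards, because a baseline taken too late cannot be recovered.

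**Conclusion.** The point holds as an internal contradiction at both time points of both primary outcomes, and it should be corrected. What is established is that contamination of the pre-post change can occur, not that it has. Its net direction is not fixed: a late baseline would tend to shrink the change, and an in-session post survey could inflate it. Its size cannot be derived from the protocol.

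Under the stated assumptions, a modest net upward shift would raise the chance of a significant result well above 5%: to 20% or 38% with 32 pairs, and to 16% or 29% with 24. A late baseline would instead cost power. The contradiction stands whatever values are assumed.

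**What to change.** Reconcile the Measures overview with Ethical Considerations, Procedures and Data Collection, and Study Procedures:

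1. In the Measures overview, delete the opening words that place the baseline survey in the initial session and those that place the post survey in the final CHW session.
2. State one baseline rule: self-completed on Qualtrics before the start of session 1, ideally before referral to MTS.
3. State one post-intervention rule: self-completed by link after session 6 has ended, outside any CHW session.
4. Use the Qualtrics completion times to flag any baseline completed after the start of session 1 and any post survey completed before the end of session 6. The baseline cut-off must be the start of session 1, because a cut-off at its end would miss a form completed during the session, which is the case the Measures overview describes.
5. Report which procedure applied to the 16 participants enrolled as of March 2026, and run a sensitivity analysis of the paired comparison excluding flagged surveys.

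The cost is a change of wording and a small change of workflow. Taking the surveys out of the sessions will probably need a few more reminders and may leave slightly more post surveys missing. Surveys already collected cannot be retimed, so for those participants the remedy is reporting and the sensitivity analysis.
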